**History of Protocol Modifications:**

| Version | Date | Description of Modifications |
| --- | --- | --- |
|  |  |  |
|  |  |  |

**List of Abbreviations**

- **ANSM:** National Agency for the Safety of Medicines and Health Products (Agence Nationale de Sécurité du Médicament)
- **CNIL:** National Commission on Informatics and Liberty (Commission Nationale Informatique et Liberté)
- **CPP:** Committee for the Protection of Persons (Comité de Protection des Personnes)
- **IRR:** Regional Institute of Rehabilitation (Institut Régional de Réadaptation)
- **MPR:** Physician in Physical and Rehabilitation Medicine (Médecin en Médecine Physique et de Réadaptation)
- **PMSI:** Medical Information Systems Program (Programme de Médicalisation des Systèmes d’Information)
- **RIPH:** Research Involving the Human Person (Recherche Impliquant la Personne Humaine)

**ActivTronc Protocol**

**1. Scientific Context**

Cerebral palsy (CP) describes a group of permanent motor and postural disorders that limit activity, caused by lesions to the developing brain in utero or post-partum. Subsequent reorganizations of central nervous system functions in children with CP also lead to motor disorders (1). The typical development of segmental trunk control, which occurs progressively during childhood (2), is closely linked to gross motor performance in young infants (3) and is significantly delayed in premature infants (4). From early infancy, children with CP exhibit axial control disorders and abnormal postural control in a sitting position (5). We recently showed that children with CP had specific impairments in trunk control during a self-stabilization task on an unstable sitting device compared to typically developing (TD) children (6). These deficits in axial postural control (and particularly in trunk control) remain present throughout the motor development period—even after the child can stand and walk independently (7).

During walking, children with CP show significant deviations in trunk kinematics and kinetics; the ranges of motion of the trunk in all three planes of space are much larger than in TD children (8). These deviations are associated with poor dynamic balance control during walking (9), resulting in wider step widths (10), greater variability in step length, greater accelerations of the head, thorax (upper trunk), lower back (L3 region), pelvis, and the body's center of mass in all three planes throughout the gait cycle, and greater lower back instability compared to TD children (11,12). Since the trunk and lower limbs interact reciprocally during walking, in children with CP, trunk deviations lead to lower limb deviations, and vice versa (7,13).

Toe walking is one of the most common lower limb deviations in children with CP. It is defined as the absence of the first rocker (heel rocker) when children touch the ground with a flat foot or with the forefoot at initial contact (IC) (14). Thus, IC is immediately followed by the second rocker, as the tibia rolls over the ankle. At IC, the ankle angle is often in plantar flexion, i.e., in equinus. The absence of the first rocker in children with CP is also associated with intense and early energy absorption and negative work done at the ankle joint (15), which decelerates ankle dorsiflexion and the anterior tilt of the tibia during the weight acceptance (WA) phase of walking (defined as the initial period of combined energy absorption at the lower limb joints) (16). This behavior involves early activity of the triceps surae, which begins in late swing and lasts throughout the WA phase (17). It is generally believed that prolonged activity of the plantar flexors during walking in children with CP is due to spasticity (hyperexcitable stretch reflexes) and induces equinus (1). Nevertheless, the existence and/or functional significance of exaggerated stretch reflexes during walking in spastic patients has been debated for decades (18). In particular, it is unlikely that spasticity contributes to toe walking in children with CP; soleus activity during the swing phase is reduced (15), and exaggerated reflex activity is absent (19). In contrast, toe walking in children with CP and in typically developing (TD) children is characterized by feedforward control of the ankle muscles—suggesting that this walking pattern is part of an adaptive process (20).

When the second rocker begins, the plantar flexors decelerate ankle dorsiflexion, slow the forward progression of the trunk, and support the body by accelerating it upward (21). This upward acceleration of the body can be achieved either by moving the center of mass (CoM) upward or by decelerating the downward movement of the CoM. In children with CP, the activity of the plantar flexors associated with the early second rocker in WA results in negative ankle power, which slows ankle dorsiflexion and thus decelerates the body's CoM downward and forward (22). All these actions contribute to the greater negative work done on the CoM by the leading leg in children with CP compared to TD children (23). The presence of the aforementioned trunk control disorders and impaired dynamic balance control during walking in children with CP suggests that the early activation of plantar flexors and the high negative ankle power during WA associated with toe walking could correspond to an adaptive mechanism to decelerate the forward and downward displacements of the trunk, in order to compensate for poor balance and poor postural control of the trunk.

In children with cerebral palsy (CP), aged 5 to 12 years, with impaired trunk control and independent toe walking, we recently showed, compared to TD children, a greater step width (due to impaired balance) (10), a greater peak of anterior sternum deceleration, downward sacrum deceleration, and negative ankle power during the WA phase (24) **(Figure 1).**

[figure not shown]

**Figure 1:** Mean total ankle power (A, B), mean anteroposterior acceleration of the sternum marker (C, D), and mean upward acceleration (i.e., downward deceleration) of the sacrum marker (E, F), during walking, in children with cerebral palsy (CP) who performed TFR then UR (A, C, E, n=8) or UR then TFR (B, D, F, n=9), and in TD children (all panels, n=17). TFR: trunk-focused rehabilitation (=RAIT); UR: usual rehabilitation (=RH); TD: typically developing. The black lines correspond to the CP group (solid line for M0, dotted line for M3, and dashed line for M6) and the solid gray line corresponds to the TD group at M0. The rectangle corresponds to the area of interest for the peak during the weight acceptance phase.

The peak deceleration of the sternum and sacrum were significantly correlated with the peak negative ankle power during the WA phase, which is consistent with the action of the plantar flexors on the trunk or the CoM (22,25). This cross-over study also allowed for the evaluation of the effect of a rehabilitation based on activities strongly involving the trunk (RAIT) for 3 months compared to a usual rehabilitation (RH) mainly based on conventional rehabilitation targeting muscle groups (stretching, strengthening, tone reduction) of the lower limbs. Only RAIT significantly improved trunk postural control, as evidenced by the improvement in the Trunk Control Measurement Scale score (26) and postural self-stabilization on an unstable sitting device (6). Furthermore, only RAIT significantly reduced the peaks of sternal and sacral deceleration and the coupled negative ankle power in the WA phase (see Figure 1). It is thus strongly suggested that the plantar flexors compensate for impaired trunk postural control—a key target of rehabilitation in children with CP.

Therefore, there is a strong interest in rehabilitating the trunk in children with CP. Indeed, while our study shows benefits on parameters related to dynamic balance during walking, many other studies have made the trunk the main target of their intervention (27–32). These studies notably show an improvement in trunk control, but also in walking (spatio-temporal parameters, performance on the Timed-Up-and-Go, the 1-minute walk test, and the 6-minute walk test) as well as gross motor function. Moreover, studies that have tested hippotherapy protocols in children with CP link the observed improvements in balance, walking, and gross motor function with the improvements induced in trunk control (33–36).

Due to the importance of trunk control on the gross motor function, balance, and walking of children with CP, and given all the studies showing the benefit of a trunk-focused rehabilitation, trunk-focused rehabilitation protocols are now prescribed to patients in our center whose profile seems to indicate an interest in trunk strengthening. The study of the effect of RAIT on the ability to stabilize in an unstable sitting position and on the dynamics of the trunk and ankle during walking, which we conducted, was carried out in children with CP aged 5 to 12 years, partly due to technical limitations related to the unstable seat and the three-dimensional motion analysis with many markers to be placed on the skin, which are difficult to perform on children under 5 years of age. However, it seems relevant to carry out a rehabilitation like RAIT early, from the age of 18 months, to improve postural balance control and walking dynamics in children with CP.

With this in mind and to simplify the functional exploration of walking dynamics, and to be able to evaluate the effects of the RAIT prescribed to our youngest patients, we have acquired inertial measurement units to measure the deceleration of the sternum and the sacrum (L5) and a pressure-sensitive walkway (**Figure 2**) to analyze gait instability via spatio-temporal parameters and to measure, at the beginning of the stance phase, the extent of the early forward shift of the plantar pressure associated with the toe-walking pattern. The analysis of postural control of standing is also simplified through the use of an inertial measurement unit placed at L5 to estimate the displacements of the body's center of mass (mSway software). Clinical scores are also used for an assessment of balance and global functional motor skills. Furthermore, RAIT has other potential benefits such as an improvement in the functional use of the upper limb and hand, observed on the sidelines of the study in children aged 5 to 12 years (24). Also, in this study we explore the motor function of the upper limb and hand via a questionnaire addressed to the parents.

[figure not shown]

**Figure 2:** Walkway equipped with relative pressure sensors (Zeno®) allowing for an extended and simplified analysis of spatio-temporal parameters and the dynamics of plantar footprints

**2. Objective(s), Endpoint(s), and Hypothesis(es) of the Study**

**2.1. Primary Objective and Hypothesis**

The primary objective of the study is to show that the RAIT protocol, prescribed over a 3-month period, and not a usual rehabilitation (RH), reduces the peak forward deceleration of the sternum at the beginning of the stance phase (the first 25% of the gait cycle) in children with CP aged 18 months to 5 years and 6 months who walk independently or with intermittent use of a walking aid (walker, crutches, etc.), which corresponds to levels I to II of the Gross Motor Function Classification System (GMFCS) (37). Children who intermittently use a walking aid must be able to walk independently for a distance of about 10 m to allow for assessment on the walkway.

**2.2. Primary Endpoint**

Peak forward deceleration of the sternum during the first 25% of the gait cycle.

**2.3. Secondary Objective(s) and Hypotheses**

The secondary objectives, for the secondary endpoints described in paragraph 2.4 below, aim to: (1) show an impairment of these criteria in the study's children with CP compared to typically developing (TD) children; (2) show a significantly greater improvement in these criteria after 3 months of RAIT than after 3 months of RH; (3) show a further improvement in these criteria when the duration of RAIT is increased.

**2.4. Secondary Endpoints**

(1) Variables related to the quality of spontaneous walking:

- Peak downward deceleration of L5 during the first 25% of the gait cycle
- Percentage of load on the anterior half of the foot during the first double support phase
- Step width normalized to pelvis width
- eGVI: enhanced Gait Variability Index (38,39)

(2) Variables related to postural control of standing:

- Mean velocity of horizontal displacement of the body's center of mass
- 95% confidence ellipse of the area of horizontal displacement of the body's center of mass

(3) Functional variables assessed by clinical scores:

- Score on the Early Clinical Assessment of Balance (ECAB) (40)
- Score on the Gross Motor Function Measure 66 Item Set (GMFM 66 IS) (41)
- Edinburgh Visual Gait Score (42)

**3. Methodology**

**3.1. Study Type**

Single-center randomized controlled interventional study.

**3.2. Study Population**

Children with cerebral palsy presenting with gait pattern disorders seen in outpatient consultation and/or treated (day or full hospitalization) at the CMPRE of Flavigny-sur-Moselle. Cerebral palsy is a long-term condition requiring well-codified specialized medical follow-up. In the Lorraine region, the multidisciplinary therapeutic follow-up of this population is coordinated by a network of physicians specializing in physical and rehabilitation medicine, neuro-pediatrics, and pediatrics working in several institutions. The children with CP recruited for this study will be children with spastic hemiplegia or diplegia, with independent walking without a walking aid (GMFCS I to II). In the case where the child has diplegia, only the lower limb with the most spastic soleus will be analyzed. The most spastic soleus is defined as the one for which the greatest difference is observed between the range of slow passive dorsiflexion movement and the angle obtained using the maximum dorsiflexion speed V3, according to the Modified Tardieu Scale (43).

**3.2.1. Inclusion Criteria**

**For children with CP:**

- Age between 18 months and 5 years and 6 months
- CP of spastic diplegia or spastic hemiplegia type, GMFCS I to II
- No or moderate contracture of the triceps surae (ankle dorsiflexion: > 5° during clinical examination, knee extended)
- Sufficient level of understanding to perform the activities involving the trunk in the form of self-exercises (rehabilitation protocol) as well as the clinical assessments and functional explorations.
- Acceptance of the physical therapist in charge of the child's follow-up to collaborate in the implementation of the RAIT
- Affiliated with a social security scheme

**For TD children:**

- Age between 18 months and 5 years and 6 months
- Walking acquired before the age of 18 months
- Sufficient level of understanding to perform the clinical assessments and functional explorations
- Affiliated with a social security scheme

**3.2.2. Non-Inclusion Criteria**

**For children with CP:**

- Previous lower limb surgery within the last year
- Botulinum toxin A injection within the last 6 months
- Any change in rehabilitative and/or orthopedic management within the last 2 months
- Hip flexion contracture > 20°
- Presence of subacute or chronic pain during standing or walking

**For TD children:**

- Neurological and/or orthopedic disorder that could influence walking

**3.2.3. Sample Size Calculation**

The calculation of the number of subjects needed is based on the primary endpoint. The distribution of the peak sternum deceleration at the beginning of the stance phase was Gaussian in our previous study. On average, this distribution was centered on 3.0 ± 1.1 m.s-2 (mean ± 1 standard deviation) in children with CP and on 1.1 ± 0.3 m.s-2 in TD children (24). The expected effect of RAIT is a minimum reduction in the peak sternum deceleration at the beginning of the stance phase of one-third of its value, similar to the effect of RAIT in the previous study (24). To demonstrate an effect of RAIT using a repeated measures ANOVA in which we expect a small effect size, with an alpha level set at 0.05 and a power of 80%, a total sample size of 24 patients, i.e., 12 per group, is necessary (calculation performed using G*Power 3.1 software; **Figure 3).** We expect greater variability in dynamic gait variables (expected in children aged 18 months to 5 years and 6 months compared to children aged 5 to 12 years). Therefore, we plan to recruit 32 children with CP (16 per group), to account for this greater variability and to compensate for potential dropouts.

[figure not shown]

**Figure 3:** Calculation of the number of subjects needed, performed using G*Power 3.1 software.

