**3.4. Experimental Plan**

The project includes a clinical examination and instrumental functional explorations at four time points. The experimental plan is shown in Figure 4. The assessments are described in chapter "4.3. Measurements – Description of assessments performed during the research." Assessments will be conducted at M0, M3 (M0 + 3 months), M6 (M0 + 6 months), and M12 (M0 + 12 months) for children with CP and at M0 for TD children. Thus, three rehabilitation periods will be planned: the first between M0 and M3, the second between M3 and M6, and the third between M6 and M12. A first group of children (group PC1) will continue their usual rehabilitation (RH) for the first 3 months and then will have RAIT for the following 9 months (PC1 = RH-RAIT). The second group of children, PC2, will immediately have RAIT for the 12 months of the study (PC2 = RAIT-RAIT). As the previous study conducted in children with CP aged 5 to 12 years showed a therapeutic effect only related to RAIT (and not to RH), RAIT will be continued for the children who benefited from it from the first 3-month period and for all children for the last 9 months of the study. Such a plan will allow to: 1) ensure that all children with CP benefit from RAIT; 2) measure the effect of RAIT over 3 months compared to that of RH; 3) test the reproducibility of the effect of RAIT over 3 months between the two groups and 4) test the effect of an additional 3 months of RAIT in the PC2 group (M6 versus M3) and 6 months in both groups (M12 versus M6) (**Figure 4**).

[figure not shown]

**Figure 4:** Experimental plan of the study. RAIT: rehabilitation through postural activities involving the trunk; conventional rehabilitation is based on the treatment of muscle groups (stretching, strengthening, tone reduction) of the lower limbs

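### The 24 children said to give 80% power for a small effect do not follow from a small effect, and the protocol's own one-third effect reaches 80% at 24 only if repeated measures correlate at about 0.7 or more

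*Protocol*

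**What the plan says.** Section 3.2.3 of the protocol gives three things in one paragraph.

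- The natural-scale inputs. Peak sternum deceleration in the earlier study was "centered on 3.0 ± 1.1 m.s-2 (mean ± 1 standard deviation) in children with CP", and the plan expects a "minimum reduction in the peak sternum deceleration at the beginning of the stance phase of one-third of its value".
- The calculation. It was made in G*Power for a repeated-measures ANOVA "in which we expect a small effect size, with an alpha level set at 0.05 and a power of 80" per cent, and returned 24 children, 12 per group. The readable text gives no numerical f, no correlation between visits and no sphericity correction. The software output is in Figure 3, which is not shown.
- The allowance. Recruitment is raised to 32 (16 per group) "to account for this greater variability and to compensate for potential dropouts", with no figure for either.

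Section 4.5 sets the analysis as a mixed design with 2 groups and 4 visits (M0, M3, M6, M12), focused on the group-by-period interaction. Section 3.4 says that the earlier study "showed a therapeutic effect only related to RAIT (and not to RH"), and that both groups receive RAIT from M3 onwards.

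**The concern.** This paragraph is the only basis for the trial's size. It describes the effect in words as small, in natural units as a one-third fall, and by implication through the number 24. These descriptions do not agree, so a reader cannot tell which effect the trial has 80% power to detect.

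Two things depend on the answer. A null result would be read against an 80% power claim whose basis is unclear. The scientific committee, which section 9.1 allows to re-evaluate the sample size, would have no coherent target to work from.

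**Working it through.** **Inputs.** From the protocol: alpha 0.05, power 80%, k = 2 groups, m = 4 visits, mean 3.0, SD 1.1, reduction of one-third, N = 24 and N = 32. Assumed: small means f = 0.10 and medium means f = 0.25 (the usual conventions); sphericity holds (epsilon = 1); the correlation ρ between visits is not in the readable text, so a range is used.

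**Formula.** Noncentral F for the group-by-period interaction, as in G*Power: λ = f²·N·m/(1−ρ), df1 = (k−1)(m−1) = 3, df2 = (N−k)(m−1), which is 66 at N = 24.

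**Step 1: the stated figure.** With f = 0.10:

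| ρ | 0 | 0.3 | 0.5 | 0.7 | 0.8 | 0.9 |
|---|---|---|---|---|---|---|
| N for 80% power | 274 | 194 | 138 | 84 | 56 | 30 |

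At N = 24 and ρ = 0.5, λ = 0.01 × 24 × 4/0.5 = 1.92 and power is 18% (23% at N = 32). The stated 24 is not reproduced.

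**Step 2: what does give 24.** With f = 0.25 and ρ = 0.5, λ = 0.0625 × 24 × 4/0.5 = 12.0 and power is 81.6%; N = 24 is the smallest even total that reaches 80%. A small effect gives the same λ only when 0.01/(1−ρ) = 0.0625/0.5 = 0.125, that is, ρ = 0.92.

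**Step 3: the protocol's own effect.** One-third of 3.0 is 1.0 m/s², so at M3 d = 1.0/1.1 = 0.91. For the interaction, take usual rehabilitation as having no effect and the RAIT effect as held once reached. The expected means are 3, 3, 2, 2 for PC1 and 3, 2, 2, 2 for PC2. After removing group and visit means, the residuals are ±0.375 at M3 and ±0.125 at the other three visits. Their root mean square is √[(2 × 0.375² + 6 × 0.125²)/8] = √0.0469 = 0.2165, and f = 0.2165/1.1 = 0.197.

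At N = 24 and ρ = 0.5, λ = 0.197² × 24 × 4/0.5 = 7.4. Over the range:

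| ρ | 0.3 | 0.5 | 0.6 | 0.7 |
|---|---|---|---|---|
| Power, N = 24 | 44% | 59% | 70% | 83% |
| Power, N = 32 | 57% | 74% | 84% | 93% |
| N for 80% power | 52 | 38 | 30 | 24 |

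At N = 24 the 80% line is crossed at ρ of about 0.68.

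**Step 4: the allowance.** Required N scales with variance. Going from 24 to 32 therefore absorbs an SD rise of √(32/24) = 1.155, about 15% (SD 1.27), with no dropouts; √(28/24) = 1.08, about 8%, with four dropouts; and none with eight. By the same formula, for ρ = 0.3, 0.5 and 0.7:

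- 28 evaluable, SD 1.1: 51%, 67% and 89%.
- 32 evaluable, SD 1.27 (f = 0.2165/1.27 = 0.170): 45%, 60% and 84%.

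**The case against.** The strongest defence is that the correlation is unknown to the reader and may be in Figure 3. At a correlation of about 0.7, which is not implausible, the one-third effect itself needs exactly 24 children, so 80% at 24 can be obtained from the protocol's own target. The trial also recruits 32 rather than 24, and one-third is described as the minimum expected reduction, so these powers are at the floor of what is expected. All of this stands.

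It is also fair that setting d = 0.91 against the word small mixes two scales. On the interaction scale the same effect is f = 0.197, between the conventional small and medium values. What remains is that 0.197 is about twice the conventional small value, and that 24 does not come from a small effect at any ordinary correlation. The match to f = 0.25 is an inference and is not unique, since f = 0.197 at correlation 0.7 also gives 24.

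Three stronger readings are tempting, and the documents do not support them.

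- That power at 24 simply is 57% to 59%. The 59% is the interaction at a correlation of 0.5; the 57% is an unadjusted M3 comparison, which is not the planned analysis. With the correlation unstated, power at 24 is undetermined.
- That the trial is underpowered. At 32 children, power for the one-third effect exceeds 80% at correlations of 0.6 and 0.7, before dropouts or a larger SD.
- That the allowance cannot serve both of its purposes. It covers an 8% SD rise together with four dropouts. The fault is that neither purpose is quantified.

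**Conclusion.** The sample-size statement is wrong as written: a small effect and 24 children do not go together for the planned interaction unless the correlation is about 0.92. At a correlation of 0.5, the gap is 138 children against 24, or 18% power against 80%. This rests on f = 0.10 as the meaning of small and on epsilon = 1.

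For the one-third effect, the 80% claim at 24 is conditional: it holds only if the correlation is about 0.7 or higher, assuming no effect of usual rehabilitation and a RAIT effect that is maintained. The defect lies in the stated justification. It does not show that the number of children must change.

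**What to change.** Amend section 3.2.3 as follows.

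- Delete the small-effect wording and state the target as a 1.0 m/s² difference between groups at M3 with an SD of 1.1.
- Give in the text the f, the correlation with its source, the epsilon and the model term that were entered in G*Power.
- Report the power that the fixed 32 children deliver for the section 4.5 analysis over a range of correlations, with a reduced evaluable number and a larger SD (for example 28 evaluable, and SD 1.27). This replaces the unquantified allowance for variability and dropouts.
- If a baseline-adjusted M3 comparison is quoted instead (82% at 32 children for correlation 0.5, 74% for 0.3), name that analysis in section 4.5 as well, so that the two sections agree.

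The cost is a one-paragraph amendment, with a matching line in section 4.5 if the analysis quoted there changes, and possibly a less favourable stated power. No extra children are enrolled and no treatment or visit changes.
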